## Abstract

**Background:**

Post-COVID-19 condition refers to persistent or new onset symptoms occurring three months after acute COVID-19, which are unrelated to alternative diagnoses. Symptoms include fatigue, breathlessness, palpitations, pain, concentration difficulties ("brain fog"), sleep disorders, and anxiety/depression. The prevalence of post-COVID-19 condition ranges widely across studies, affecting 10–20% of patients and reaching 50–60% in certain cohorts, while the associated risk factors remain poorly understood.

**Methods:**

This multicentre cohort study, both retrospective and prospective, aims to assess the incidence and risk factors of post-COVID-19 condition in a cohort of recovered patients. Secondary objectives include evaluating the association between circulating SARS-CoV-2 variants and the risk of post-COVID-19 condition, as well as assessing long-term residual organ damage (lung, heart, central nervous system, peripheral nervous system) in relation to patient characteristics and virology (variant and viral load during the acute phase). Participants will include hospitalised and outpatient COVID-19 patients diagnosed between 01/03/2020 and 01/02/2025 from 8 participating centres. A control group will consist of hospitalised patients with respiratory infections other than COVID-19 during the same period.

Patients will be followed up at the post-COVID-19 clinic of each centre at 2–3, 6–9, and 12–15 months after clinical recovery. Routine blood exams will be conducted, and patients will complete questionnaires to assess persisting symptoms, fatigue, dyspnoea, quality of life, disability, anxiety and depression, and post-traumatic stress disorders.

**Discussion:**

This study aims to understand post-COVID-19 syndrome's incidence and predictors by comparing pandemic waves, utilising retrospective and prospective data. Gender association, especially the potential higher prevalence in females, will be investigated. Symptom tracking via questionnaires and scales will monitor duration and evolution. Questionnaires will also collect data on vaccination, reinfections, and new health issues. Biological samples will enable future studies on post-COVID-19 sequelae mechanisms, including inflammation, immune dysregulation, and viral reservoirs.

**Trial registration:**

This study has been registered with ClinicalTrials.gov under the identifier NCT05531773.

**Supplementary Information:**

The online version contains supplementary material available at 10.1186/s12879-023-08595-0.

## Introduction

The coronavirus disease 2019 (COVID-19) pandemic has caused widespread morbidity and mortality worldwide, with over 5 million deaths attributed to the acute syndrome caused by the severe acute respiratory syndrome coronavirus 2 (SARS-CoV-2) virus [1].

However, the long-term consequences of COVID-19, also known as post-acute sequelae of COVID-19 (PASC) or long-COVID, are also concerning [2–4]. These long-lasting symptoms may include fatigue, muscle weakness, shortness of breath, cough, joint pain, chest pain, anosmia or dysgeusia, cognitive dysfunctions, sleep disorders, anxiety and depression. These symptoms may be new, following initial recovery from the acute COVID-19 illness, or may persist from the beginning of the disease. In October 2021, the World Health Organization (WHO) identified the “post COVID-19 condition” as the presence of symptoms usually three months after the onset of COVID-19 that last for at least two months and cannot be explained by a different diagnosis. Patients may also be diagnosed with residual organ damage after acute COVID-19, particularly in the lungs, heart, central nervous system, and peripheral nervous system.

Preliminary data have shown a high prevalence of post-COVID-19 condition, although there is considerable variation among different studies. This variation can be attributed to the utilisation of different definitions for post-COVID-19 condition, inclusion of diverse populations, and the use of varying or non-standardised methods to assess the persistence of symptoms.

A recent systematic review of 20 observational studies, comprising 5,440 enrolled patients, reported a prevalence of post-COVID-19 condition between 4.7% to 80% [5]. Several studies have demonstrated high rates of ongoing symptoms after hospital discharge for acute COVID-19 illness (87% after two months and 70% after six months) and in outpatient COVID-19 subjects (32% at 30–45 days from the acute episode) [6–8]. A systematic review of 57 studies, comprising more than 250,000 patients recovered from COVID-19, showed that 54% of patients reported at least one post-acute sequelae at one month (short-term), 55% at 2–5 months (intermediate term), and 54% at 6 or more months (long-term) [9].

As previously mentioned, identifying risk factors for this long-term condition is a challenging task due to the abundance of studies conducted in various settings and populations. There is conflicting evidence regarding the possible association between disease severity during the acute phase and the risk of developing post-COVID-19 condition [10–12]. Similarly, there is no consensus on the possible role of several other factors, such as acute symptoms, female gender [13], older age, smoking, body mass index, and pre-existing comorbidities, on development of SARS-CoV-2 sequelae.

The possible predictors of post-COVID-19 condition include the severity of disease, the presence of hyperinflammation or autoimmune responses, and persistent viremia during the acute phase.

Additionally, viral variants may differently affect post-COVID-19 condition, with the effect of new variants on transmission rate, immune evasion, and incidence of post-acute sequelae still to be understood [14].

Several indirect effects of acute COVID-19 could also affect post-COVID-19 condition, such as a long time of hospitalisation and home isolation, economic damage and loss of job.

## Methods and analysis

### The EuCare Project

The European cohorts of patients and schools to advance response to epidemics (EuCARE) project is a collaborative effort between several cohorts of patients and schools across various geographic regions, including European and extra-European countries (www.eucareresearch.eu). The project aims to provide an advanced response to COVID-19 epidemics by consolidating or expanding interactions among different clinical and research centres.

The project brings together a comprehensive, multidisciplinary team of clinicians, virologists, epidemiologists, statisticians, and experts in machine-learning. The primary aim of the study is to examine various facets of the COVID-19 pandemic. These include studying natural and vaccine-induced immunity to different viral variants among healthcare workers, tracking the clinical progress and long-term outcomes of COVID-19 patients admitted to hospitals, and identifying effective strategies to assist schools during similar COVID-19 outbreaks [15]. One of the key areas of investigation will be the post COVID-19 condition.

As part of the EuCARE project, Work Package 3 (WP3) has been designed to investigate the impact of COVID-19 on both hospitalised and outpatient populations. WP3 includes two distinct cohorts: the EuCARE-HOSPITALISED Study, which is currently collecting data from COVID-19 patients during the acute phase of hospitalisation, and the EuCARE POSTCOVID Study, whose aim is to gather data on post-COVID-19 conditions from both hospitalised and outpatient COVID-19 patients. The focus of this paper is the EuCARE-POSTCOVID Study, and we present its protocol here.

### Study hypotheses

The main EuCARE-POSTCOVID Study hypothesis is that a significant proportion of patients who recover from acute COVID-19 will experience long-term sequelae characterised by the presence of physical and/or psychological symptoms persisting for at least three months after the acute illness. Initial evidence suggests that patients experiencing persistent symptoms at 4–8 weeks after acute disease were more likely to be elderly, female, and hospitalised during the acute phase [16], in line with this EuCARE-POSTCOVID Study which also hypothesises that older age, female gender, higher severity of disease, and patients' comorbidities could be risk factors for the development of post COVID-19 condition.

Finally, the study hypothesis is that the Omicron variant of SARS-CoV-2 could be associated with lower incidence of post-COVID-19 condition, possibly as a reflection of lower inflammation and disease severity during the acute phase of disease. Moreover, the type and breakthrough infectivity rates of SARS-CoV-2 variants among fully vaccinated individuals may modify the incidence and manifestation of post-COVID-19 condition [9, 17]. Thus, the evaluation of circulating SARS-CoV-2 variants is crucial in predicting their potential association with post-COVID-19 condition.

### Study objectives

The primary objective of the study is to assess the incidence and risk factors of post-COVID-19 condition in a cohort of recovered COVID-19 patients.

The secondary objectives of the study are as follows:To evaluate the association between circulating SARS-CoV-2 variants and the risk of post-COVID-19 condition.To identify different clinical phenotypes of post-COVID-19 condition.To evaluate the long-term residual organ impairment, specifically of the lung, heart, central nervous system, and peripheral nervous system, in relation to patient demographic and clinical characteristics such as age, gender, comorbidities, severity of disease, and virology including viral variant, specific mutations, and viral load in the acute phase.To compare the incidence of post COVID-19 condition between males and females.

## Expected outcomes

The expected outcomes of this study include:Determination of the overall incidence of post-COVID-19 condition in the study cohort.Identification of patients who continue to experience symptoms beyond 2–3 months from the acute COVID-19 disease.Identification of cluster of symptoms that identify different clinical phenotypes of post-COVID-19 condition.Identification of predictors of post-COVID-19 condition, such as demographic, clinical, and virological factors.Evaluation of long-term organ damage associated with post COVID-19 condition, specifically in the lungs, heart, central nervous system, and peripheral nervous system.Characterisation of the virological and immunological phenotype of post-COVID-19 condition, which can provide insight into the mechanisms underlying this condition.

### Study design

This is an observational retrospective and prospective, multicentre, cohort study. The study will last for 3 years, from February 2022 to February 2025.

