### Study population

The study will enrol adult patients (> 18 years old) diagnosed with acute COVID-19 disease between 01/03/2020 and 01/02/2025 at the participating centres. The COVID-19 patients will be divided into two groups: Group 1 (hospitalised) and Group 2 (outpatients).

Inclusion criteria for the study require a confirmed diagnosis of SARS-CoV-2 infection based on a positive SARS-CoV-2 RNA test on nasopharyngeal swab or other respiratory samples. Mild COVID-19 disease is defined as cases without hospital admission, while moderate/severe disease includes cases requiring hospitalisation for COVID-19 or hospitalisation for other medical issues with a positive SARS-CoV-2 RNA sample. Patients must provide informed consent for the study to be eligible for inclusion.

Exclusion criteria include death during hospitalisation and patient refusal to participate.

The study will also enrol a control group of hospitalised patients for respiratory infections other than COVID-19 disease during the same study period, with enrolment occurring at hospital discharge and follow-up appointments scheduled at the post COVID clinic with the same timing as COVID-19 patients. These patients will be enrolled if they are adults hospitalised for respiratory infections requiring any type of oxygen therapy or Intensive Care admission (Fig. 1).

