### Patient assessment and follow-up protocol

The patient assessment and follow-up protocol for acute COVID-19 disease involves follow-up visits at 2–3, 6–9, and 12–15 months after clinical recovery. At each visit, routine blood exams and medical visits will be conducted, along with several assessments via questionnaires, including the short version of the post COVID-19 WHO Case Report Form (WHO CRF) for collection of symptoms and newly emerged complaints after COVID-19, the Fatigue Numerical Rating Scale, the Medical Research Council (MRC) dyspnoea scale, the 5-level EQ-5D test (EQ5D-5L), the 12-item WHO Disability Assessment Schedule (WHODAS), the Montreal Cognitive Assessment (MOCA), the Hospital Anxiety and Depression Scale (HADS-A/D), and a screening tool named PCL-5 for Post-Traumatic Stress Disorder (PTSD). If patients are unable to attend the post-COVID-19 clinic, the questionnaires will be able to be completed through a phone interview. All questionnaires will be standardized and available in multiple languages (Fig. 1).

Further instrumental diagnostic evaluations such as diffusing capacity of lung carbon monoxide (DLCO), spirometry, lung computed tomography (CT) scans, pneumological evaluation, echocardiography, cardiological evaluation, neurological evaluation, rehabilitation medicine specialist examination, and psychological evaluation will be conducted as necessary.

Pulmonary symptoms are common after the acute phase, thus patients undergo the MRC dyspnoea scale and oxygen saturation measurement at each post-COVID visit. Further evaluations such as chest CT scans, diffusing capacity of lung carbon monoxide (DLCO), spirometry, and a complete pneumological evaluation will be performed if oxygen saturation is < 95% or MRC dyspnoea scale grade is 2–5.

Patients who recovered from acute COVID-19 disease could present a higher risk of cardiac diseases, including heart failure, myocardial infarction, and arrhythmia in the mid- and long-term [18]. During the scheduled post-COVID visits, patients undergo a complete medical examination, including heart rate and blood pressure measurement, and fill in the MRC dyspnoea scale. Further evaluations such as an electrocardiogram, a cardiologic visit, and an echocardiography will be performed as necessary.

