## Discussion

The EuCARE project comprises several patient cohorts and schools that provide an advanced response to COVID-19 epidemics. The EuCARE-POSTCOVID study is responsible for investigating the characteristics of the post COVID-19 condition, which seems to affect up to 10–15% of patients, according to a recent review [22]. Despite the current reduction in the incidence and severity of acute SARS-CoV-2 infections in Europe, the post-COVID-19 condition remains a medical challenge. The clinical course of the syndrome, its possible risk factors, and the best diagnostic-therapeutic approach are not yet entirely understood. First data shows that the symptoms could last for one year or more.

A large group of definitions has been proposed and adopted by different research groups to indicate the failure to return to a pre-COVID state of health. We will use the 2021 definition of post-COVID-19 condition identified by the WHO because it appears to be the most standardised and globally applicable definition so far. This definition will allow us to compare our data with those of other similar cohorts [13, 16, 23, 24]. Since the WHO definition includes any symptoms that don't have an alternative diagnosis, it is quite nonspecific and could cause an overestimation of COVID-19 sequelae. We will also focus on possible clusters of symptoms identifying phenotypes of post-COVID-19 condition. This study will focus on understanding the incidence and predictors of post-COVID-19 syndrome by comparing the different pandemic waves, thanks to the long duration of the study and the possibility of including retrospective data from the beginning of the epidemics.

Among predictors, the association between gender and post-COVID-19 syndrome will be explored. Our preliminary data and previous cohorts have underlined a possible higher prevalence of the condition in females, though the reason for this association is not known [13].

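### Wave and variant comparisons pool outcomes collected before and after the February 2022 opening, so collection mode is tied to wave and no planned analysis separates the two

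*Protocol article*

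**What the plan says.** Study design: "The study will last for 3 years, from February 2022 to February 2025". Study population admits adults "diagnosed with acute COVID-19 disease between 01/03/2020 and 01/02/2025 at the participating centres", so eligibility starts 23 months before the study does. Outcomes are taken at "follow-up visits at 2–3, 6–9, and 12–15 months after clinical recovery" (Patient assessment and follow-up protocol).

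The Discussion aims at "understanding the incidence and predictors of post-COVID-19 syndrome by comparing the different pandemic waves" and counts as an advantage "the possibility of including retrospective data from the beginning of the epidemics". The abstract likewise describes the wave comparison as using both kinds of data. A secondary objective is "To evaluate the association between circulating SARS-CoV-2 variants and the risk of post-COVID-19 condition", and the sample size in Data analysis rests on Omicron versus Delta, with a 25% risk reduction to be detected. The Discussion adopts the WHO definition, which the Introduction dates to October 2021.

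Data analysis plans logistic regression adjusted for possible confounders, and inverse probability weighting for attendance at the post-COVID visit in hospitalised patients only. Neither that section nor Possible study strengths and limitations mentions whether a visit was retrospective or prospective.

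For controls, Study population provides for inclusion "with enrolment occurring at hospital discharge and follow-up appointments scheduled at the post COVID clinic". The abstract places them in the same period as the COVID-19 patients, directly after giving the 2020 to 2025 dates.

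**The concern.** A comparison of waves or variants is interpretable only if the outcome is ascertained alike in the groups compared. Here the recovery date decides whether a visit could have been made under the study at all. Early patients contribute what was recorded before the study existed, or what they recall later. Later patients can be seen on schedule with the study questionnaires. If the two sources capture symptoms differently, a rise or fall in incidence across waves may reflect the source and not the virus.

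The outcome is sensitive to this. It depends on symptom timing, on duration and on the absence of another diagnosis, and for the earliest patients the visit windows had closed before the definition was issued. The comparison at stake includes the one that sized the study.

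**Working it through.** The plan gives no figure for the share of retrospective outcomes, so there is none to reproduce. Its 90% power statement is not an input; only the 25% reduction is used, as a yardstick.

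**Inputs.** Opening taken as 01/02/2022 (the text gives the month only). Diagnosis window 01/03/2020 to 01/02/2025, which is 1,798 days. Visit windows of 2–3, 6–9 and 12–15 months after recovery. Lag from diagnosis to recovery set to zero (assumption); a longer lag moves every cut-off below to an earlier diagnosis date.

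**Step 1: window closed before opening.** This holds when recovery date + upper limit falls before 01/02/2022.
- T1: 01/02/2022 − 3 months = 01/11/2021. Days from 01/03/2020: 610; 610/1,798 = 33.9%.
- T2: − 9 months = 01/05/2021. 426/1,798 = 23.7%.
- T3: − 15 months = 01/11/2020. 245/1,798 = 13.6%.

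These are shares of calendar time, not of patients; enrolment by period is not given.

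**Step 2: window wholly after opening.** This needs recovery date + lower limit on or after 01/02/2022.
- T1: − 2 months = 01/12/2021.
- T2: − 6 months = 01/08/2021.
- T3: − 12 months = 01/02/2021.

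Between the Step 1 and Step 2 dates a window straddles the opening, and only late attenders can be prospective.

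**Step 3: link with wave.** Diagnosed before about November 2020: all three windows closed, so every outcome is retrospective. For example, recovery in March 2020 puts T3 at March to June 2021. Diagnosed from about November 2020 to October 2021: T1 closed, T2 closed for those before May 2021, T3 at least partly open, so the sources are mixed. Diagnosed from December 2021: all windows fall after opening.

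**Step 4: do the planned methods deal with it?** The weights model the probability of being sampled for the visit. They address who is seen, not how the outcome was obtained, and cover hospitalised patients only. Confounder adjustment is generic and does not name collection mode. Neither corrects a difference in outcome measurement between waves.

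**Step 5: illustration of size.** Let *f* be the share of Delta outcomes that are retrospective and *s* the capture of cases by retrospective relative to prospective collection. All Omicron outcomes are taken as prospective. Then

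apparent RR = true RR / (f·s + 1 − f).

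| f | s | Divisor | Apparent RR, true 1.00 | Apparent RR, true 0.75 |
|---|---|---|---|---|
| 0.5 | 0.85 | 0.925 | 1.08 | 0.81 |
| 0.5 | 1.15 | 1.075 | 0.93 | 0.70 |
| 1.0 | 0.75 | 0.75 | 1.33 | 1.00 |
| 1.0 | 1.25 | 1.25 | 0.80 | 0.60 |

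Both *f* and *s* are assumed. Values of *s* above 1 are included because Possible study strengths and limitations itself expects symptom-free patients to skip visits, so earlier clinic records could over-represent cases.

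**The case against.** The design is openly called retrospective and prospective, and nothing says that visits before 2022 used other instruments or ran off schedule. The questionnaires are described as standardised, and the Discussion mentions preliminary data, so some centres were already collecting. The WHO definition can be applied afterwards to dated symptom records. Source flags and sensitivity analyses are often left to the case report form or the analysis plan, neither of which is shown.

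Much of this stands. It means that bias is possible, not demonstrated, and that neither its size nor its direction is known. It does not remove the structural link between recovery date and collection mode, or supply a planned analysis that separates them. The source of a visit also has to be recorded at data entry: an analysis plan written later cannot recover it.

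Stronger readings are tempting, and the documents do not support them.
- A reader might infer that data source coincides with wave throughout. It does so only for the earliest patients. How far Delta and Omicron differ in source is an assumption, because no wave dates are given.
- A reader might infer that COVID-19 patients will be compared with controls from a different calendar period. No COVID-versus-control analysis appears under Study objectives or Data analysis. That no controls exist before February 2022 follows from enrolment at discharge but sits against the abstract's same-period wording; it is a discrepancy to resolve, not an established gap.
- A reader might take isolation, economic damage and job loss as period influences that need concurrent controls. The Introduction calls them indirect effects of acute COVID-19.

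**Conclusion.** The point holds in this form: the plan compares waves and variants on pooled data in which collection mode is tied to wave, and no stated method handles a difference in outcome collection. The date cut-offs follow from the documents' own figures, given an opening at 01/02/2022 and no recovery lag. By calendar time, T1, T2 and T3 had closed before opening for 33.9%, 23.7% and 13.6% of the diagnosis window.

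The risk ratios above show a range under assumed inputs and are not estimates. At the extreme (every Delta outcome retrospective, capture 25% lower) the targeted 25% reduction would vanish; with over-capture it would be exaggerated. The change should be made, with medium confidence in its practical importance, because the instruments used before 2022 and the wave dates are not stated.

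**What to change.** 1. Record for each visit whether it was collected prospectively with the study case report form or taken from earlier records.
2. Report incidence separately by data source.
3. Accompany the wave and Omicron-versus-Delta comparisons with a pre-specified analysis limited to the same visit collected prospectively in both groups. Let the per-visit flag decide inclusion, not a calendar cut-off. A cut-off at May 2021 for T2 or November 2020 for T3 would be too early, because at those dates the window is only just closing when the study opens; windows lie wholly after opening from about August 2021 and February 2021 respectively.
4. Draw a wave or variant conclusion only if this analysis and the pooled one agree.
5. Reconcile the abstract's period for controls with their enrolment at hospital discharge. Limit any COVID-versus-control comparison to hospitalised COVID-19 patients discharged in the calendar period in which controls were actually enrolled.

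The cost is one data field per visit and some analysis wording, with no new visits. The restricted analysis loses precision and the earliest patients, and T2 and T3 carry more attrition than T1. Making it the sole primary analysis would be a debatable trade-off, so it is proposed alongside the pooled one.
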